#### 7.1.1 Women of childbearing potential (WOCBP)

The inclusion of WOCBP (defined as fertile women following menarche and until becoming post-menopausal unless permanently sterile by hysterectomy, bilateral salpingectomy and bilateral oophorectomy), requires use of highly effective contraceptive measures such as:

- Combined hormonal contraception or progesterone-only hormonal contraception associated with inhibition of ovulation (oral, intravaginal or transdermal)
- Intrauterine device
- Intrauterine hormone-releasing system
- Bilateral tubal occlusion
- Vasectomized partner
- Sexual abstinence

Measures for contraception shall be maintained during treatment with IMP, and 5 months after termination of the study treatment.

### 1.3 EXCLUSION CRITERIA

- 1) The patient is, in the opinion of the investigator, assessed as unfit to receive systemic adjuvant treatment.
- 2) Serious and/or uncontrolled medical disorder that in the opinion of the investigator is contraindicated.
- 3) An active, known, or suspected autoimmune disease. Participants with type I diabetes mellitus, hypothyroidism requiring hormone replacement only and skin disorders (such as vitiligo, psoriasis, or alopecia) not requiring systemic treatment are eligible.
- 4) Life-expectancy less than 2 years due to concurrent disease (*e.g.*, cardiac disease and liver cirrhosis).
- 5) Inability to provide informed consent or refusal to do so.
- 6) Inability to comply with the study protocol.
- 7) Participation in other clinical trials interfering with the current study protocol.
- 8) Existing or previous malignancies within the past 5 years (except for [with curative intent treated](#) in situ breast and in situ

cervical cancer, melanoma in situ, malignant melanoma, non-melanoma skin cancer and low risk prostate cancer (the latter also allowed if existing)).

9) Breast-feeding, pregnancy, or planned pregnancy.

10) Ocular and mucosal melanoma.

~~The patient must be randomized and start systemic treatment within 12 weeks after final surgery, i.e. excision + sentinel node biopsy, lymph node dissection or metastasectomy. However, neoadjuvant treated patients must be randomized within 6 weeks after radical surgery.~~

## 8 STUDY PROCEDURES

### 8.1 RANDOMIZATION PROCEDURE

Randomization 1:1 will be locally performed in the electronic data capture (EDC) system (Viedoc) before start of adjuvant treatment and stratified according to tumour stage, and neoadjuvant treatment given or not, type of neoadjuvant treatment (PD-1 inhibitor or ipilimumab + nivolumab) treatment and pathological response (partial or non-response) after neoadjuvant treatment.

### 8.2 ~~8.2~~ STUDY TREATMENT

Adjuvant treatment with current standard immunotherapy drugs will be given according to the routine treatment schemes in both study arms.

~~Adjuvant +/- neoadjuvant treatment with current standard immunotherapy drugs will be given according to the routine treatment schemes in both study arms. The study treatment options are:~~

- ~~• Nivolumab given every second or fourth week at the registered dose, i.e. 240 mg or 480 mg respectively.~~
- ~~Pembrolizumab given every third or sixth week at the registered dose, i.e. 200 mg or 400 mg respectively.~~

Hybrid dosing is also an alternative which means that patients will receive an individualized dose based on weight according to Table 2 in Malmberg et al (17) and as listed below:

|                      | Hybrid dosing                                                                                   |
|----------------------|-------------------------------------------------------------------------------------------------|
| Pembrolizumab | 100 mg every 3 weeks for individuals weighing <65 kg, or 150 mg for individuals weighing ≥65 kg |

|                  |                                                                                                                                                                       |
|------------------|-----------------------------------------------------------------------------------------------------------------------------------------------------------------------|
|                  | 200 mg every 6 weeks for individuals weighing <65 kg; 300 mg every 6 weeks for individuals weighing 65-90 kg; or 400 mg every 6 weeks for individuals weighing ≥90 kg |
| Nivolumab | 3 mg/kg every 2 weeks, maximum 240 mg                                                                                                                                 |
|                  | 6 mg/kg every 4 weeks, maximum 480 mg                                                                                                                                 |

The kind of immunotherapy and the dosing interval that is to be used for an individual patient must be decided by the PI before randomization. [Subcutaneous route and bisoimilars will be allowed under the prerequisite that they are approved by the EMA.](#)

The standard treatment might change during the course of the study, based on upcoming results from ongoing phase III adjuvant studies (see above). If standard treatment is changed a protocol amendment will be issued and a substantial modification (SM) will be submitted and approved in Clinical trial information system (CTIS) before the new treatment is implemented in the study. Patients who have undergone neoadjuvant immunotherapy are also eligible for the study providing that a complete [or near complete](#) pathological response has not been achieved. ~~which usually is the case~~ [With PD-1 inhibitor as single treatment, in almost 520% of the patients experience a complete or near complete pathological response reponseases](#) (6) [while this is the case for more than 60% with combination immunotherapy](#) (7). Since the neoadjuvant treatment duration is two months, these patients will in the standard arm receive 10 months post-operative treatment and in the experimental arm, four months post-operative treatment only. ~~In case of treatment delays, the duration of treatment will not be prolonged.~~ Follow-up visits, blood tests and management of side effects will follow current practice based on national guidelines.

Expected side effects of the study treatment (refer to respective Summary of product characteristics, SmPC) will be managed according to routine clinical practice and the international guidelines for the management of immune related side effects: ASCO, ESMO and The society of immunotherapy on cancer (SITC).

Randomization 1:1

[figure not shown]

Standard treatment with checkpoint inhibitor for **10\*/12 months** (established treatment duration).

[figure not shown] Standard treatment with checkpoint inhibitor for **4\*/6 months** (experimental arm).

\*neoadjuvant treated patients

### **Patients who have not received neoadjuvant treatment**

In case of treatment delays, the duration of treatment will not be prolonged, regardless the number of treatments administered. The study treatment options are:

- Nivolumab given every fourth week (six treatments in the experimental and thirteen in the standard arm respectively) at the registered dose, i.e. 480 mg respectively.
- Pembrolizumab given every third (eight treatments in the experimental and seventeen in the standard arm respectively) or sixth week (four treatments in the experimental and nine in the standard arm respectively) at the registered dose, i.e. 200 mg or 400 mg respectively.

### **Patients who have received neoadjuvant treatment**

Usually, the stipulated number of treatments will be given on the discretion of the investigator regardless of treatment delays.

- Nivolumab given every fourth week (four treatments in the experimental and eleven in the standard arm respectively) at the registered dose, i.e. 480 mg.
- Pembrolizumab given every third (six treatments in the experimental and fifteen in the standard arm respectively) or sixth week (three treatments in the experimental and seven in the standard arm respectively) at the registered dose, i.e. 200 mg or 400 mg respectively.

## **1.3 CONCOMITANT USE OF OTHER MEDICINAL PRODUCTS AND TREATMENTS**

Medications considered necessary for the safety and well-being of the subject may be prescribed at the discretion of the investigators, unless otherwise specified in the exclusion criteria. Concomitant medication should be recorded in the Case Report Form (CRF).

## **1.4 STUDY FOLLOW-UP SCHEME**

The schedule of assessments is listed in Appendix 1.

A baseline visit 1-11 weeks after the last melanoma-related surgery is scheduled for study information, inclusion and randomization. The national routine schedule for follow-up visits will be

applied for all patients in the study according to standard practice which normally includes doctor appointments with physical examinations after each radiological assessment.

The scheme includes compulsory imaging [including brain](#) at baseline (within 4 weeks [for adjuvant and 8 weeks for neoadjuvant respectively](#) of [study treatment start](#)~~randomization and including brain~~), and at 6 and 24 months (~~including brain~~) respectively (see flow-chart below). The minimum imaging scheme is similar to Swedish guidelines but clearly less extensive than current practice in most other countries, e.g. Great Britain ([name], personal communication) and much more frequent imaging was done in previous adjuvant studies (1, 2). Swedish patients will undergo one extra scan (at 24 months) compared to national guidelines which corresponds to (Uppsala University Hospital as reference) an additional radiation dose of 12 mSievert (dose for CT scan) or 6 mSievert (dose for FDG-PET-CT). The mode of imaging (CT scan of the thorax, abdomen and brain/MRI brain or i.v. contrast enhanced whole body FDG-PET-CT including brain or whole body FDG-PET-CT and MRI brain) is chosen by the investigator at baseline and preferably, the same method is used for all imaging. Importantly, if an FDG-PET-CT without contrast or CT not including brain is conducted at 24 months, MRI of the brain must also be performed. If the primary CMM was situated on one leg, the FDG-PET-CT must include the site of the primary tumour. In case of a positive sentinel node but no performed lymph node dissection, CT imaging must include local lymph nodes.

All patients will be followed for survival for at least 5 years.

Extra diagnostic assessments (imaging and laboratory tests) should be done for all subjects presenting signs and/or symptoms of relapse at the discretion of the investigator and as per clinical practice. Patients in both groups should be instructed to contact their study center if they experience any symptoms suspicious of recurrence.

#### Flow-chart of minimum number of radiological assessments

[figure not shown]

This study will consist of 3 phases: screening, treatment, and follow-up.

## 1.5 TREATMENT IN THE CASE OF RECURRENCE

If recurrence is suspected or verified, the patient should be investigated and treated as per local practice and national guidelines. A discussion of the case at an MDT conference, in order to decide and offer the best available treatment (e.g. salvage surgery, palliative chemotherapy, checkpoint inhibitors, BRAF- and MEK-inhibitors and/or radiotherapy, experimental treatment in a study, palliative care) is encouraged. The MDT should preferably include a surgeon, a dermatologist, a pathologist, a radiologist, a contact nurse, a research nurse and an oncologist. Patients who experience [local](#) recurrence ~~and start a new treatment~~ will continue to be followed up according to the protocol for a total of five years. [Patients who experience distant relapse will continue to be followed up for survival according to the protocol for 5 years.](#)

## 1.6 START, END, TEMPORARY HALT AND EARLY TERMINATION

The start of the trial is defined as the first visit of the first subject. Sponsor will report the start of the trial in each participating country through notification in CTIS within 15 days. The trial may be prematurely terminated for safety reasons affecting the risk-benefit balance or if the recruitment of subjects cannot be completed within reasonable time. Decisions on premature termination are taken by the sponsor. The Competent Authorities will be informed as soon as possible via CTIS, but no later than 15 days after trial suspension.

If the trial is prematurely terminated or suspended, the investigator will immediately inform the subjects and ensure appropriate treatment and follow-up. On the individual level the treatment will be stopped if severe toxicity occurs, please see the international guidelines (ASCO, ESMO and SITC).

### 1.6.1 Definition of End of Trial

The trial ends when the last subject has completed the last follow-up.

## 9 EVALUATIONS

### 9.1 PRIMARY ENDPOINTS

The primary endpoints of the study are DMFS and RFS at 2 years.

## 9.2 SECONDARY ENDPOINTS

The secondary endpoints are long-term DMFS, RFS and OS. DMFS and RFS are evaluated with radiology and clinically. OS is evaluated based on survival data in patient medical records. For the secondary endpoints, the patients will be followed for OS for at least five years.

## 9.3 ADDITIONAL EVALUATIONS

Health economics will be analyzed. In particular if the experimental arm turns out as effective as standard treatment, the savings in costs will be addressed.

# 10 SAFETY REPORTING

Since the study treatment consists of well-known medicinal products that are used in the approved doses and patients in the experimental arm will receive a shorter, ie less toxic regimen than the current standard treatment, no extensive safety reporting is deemed necessary. Treatment related serious adverse events (SAE) during treatment and up to 6 months after treatment will be registered. Suspected unexpected serious adverse reactions (SUSARs) will be reported by sponsor to the authorities, according to local regulations, based on the information captured in the eCRF. (E.g. SUSARs that occur in Finland shall be reported by secure e-mail (Eudralink or Fimea's secure mail service) to [contact]. Fimea will then transfer the information to EudraVigilance on the investigator's behalf.)

## 10.1 DEFINITIONS

### 10.1.2 Serious Adverse Event (SAE)

Serious Adverse Event (SAE): Any untoward medical occurrence in a subject to whom a medicinal product is administered that at any dose requires:

- inpatient hospitalization or prolongation of existing hospitalization,
- results in persistent or significant disability or incapacity,
- results in a congenital anomaly or birth defect,
- is life-threatening, or results in death.

Medical and scientific assessment will be made to determine if an event is serious.

### 10.1.3 Suspected Unexpected Serious Adverse Reaction (SUSAR)

SUSAR: An adverse reaction/event that is unexpected, serious, and suspected to be caused by the treatment, i.e. adverse reactions/events that are not included in the Reference safety information (RSI) section of the Summary of product characteristics (SmPC).

### 10.2.1 Assessment of causal relationship

The investigator is responsible for determining whether there is a causal relationship between the AE/SAE and use of the investigational medicinal product.

Consideration should be given to whether there is a reasonable possibility of establishing a causal relationship between the adverse event and the investigational medicinal product based on the analysis of the available evidence.

All AE can be categorized as either likely related, possibly related, unlikely related or not related, in accordance with the definitions below:

**Likely related:** Clinical event, including abnormal results from laboratory analyses, occurring within a reasonable time after administration of the intervention/investigational medicinal product. It is unlikely that the event can be attributed to underlying disease or other medications but is most likely caused by the investigational medicinal product and its emergence is reasonable in relationship with use of the investigational medicinal product.

**Possibly related:** Clinical event, including abnormal results from laboratory analyses, occurring within a reasonable time after administration of the intervention/investigational medicinal product. The event could be explained by the investigational medicinal product and its emergence is reasonable in relationship with use of the investigational medicinal product, but there is insufficient information to determine the relationship. The event could be explained by an underlying disease or other medications.

**Unlikely related:** Clinical event, including abnormal responses from laboratory tests, unlikely to be related to the intervention/investigational medicinal product and can be reasonably explained by other medication or underlying disease.

**Not related:** Clinical event, including abnormal results from laboratory analyses, that is not reasonably related to the use of the intervention/investigational medicinal product.

Those AEs which are suspected of having a causal relationship to the investigational medicinal product will be followed up until the subject has recovered or is well taken care of and on the way to good recovery.

If the reporting investigator does not provide any information on causality, the sponsor should

consult with the reporting investigator and encourage the expression of a position on this issue. The sponsor must take into account the assessment of causality provided by the investigator. If the sponsor disagrees with the investigator's assessment of causality, both the investigator's and the sponsor's views should be included in the report.

### 10.2.2 REPORTING AND REGISTRATION OF SERIOUS ADVERSE EVENTS (SAE)

The investigator/[research nurse](#) ~~will~~should register and document SAEs and report them to the sponsor in the eCRF. At each contact with the investigator/nurse, trial subjects should be asked about how they have been feeling since the previous visit.

The assessment that an event is an SAE ~~as well as the registration in the SAE form in the eCRF~~ must be made by the investigator.

SAEs must be reported to the sponsor in the eCRF within 24 hours of the investigator being informed of the SAE.

Follow-up information describing the outcome and handling of the SAE is reported as soon as this information is available. Any original SAE documents should be kept in the Investigator Site File.

## 10.2 SUSAR

Those SAE which are assessed by sponsor to be SUSARs are to be reported to the EudraVigilance database. The completed CIOMS form will be the basis for the reporting in the EudraVigilance database according to the specified time frames.

SUSAR that are fatal or life-threatening are reported as soon as possible and no later than 7 days after the SAE has become known to the sponsor. Relevant follow-up information is sent thereafter within an additional 8 days. Other SUSAR are reported as soon as possible and no later than 15 days after they have come to the sponsor's knowledge.

Information about SUSAR occurring during the trial is compiled by the sponsor and sent to the principal investigators at all participating sites.

## 11 STATISTICAL METHODS

The efficacy analyses of DMFS and RFS will include all per-protocol patients (intention-to-treat population for sensitivity analysis). DMFS is defined as the time from start of treatment to detection

of distant relapse or death and RFS as the time from start of treatment to detection of relapse (local, regional or distant) or death. Kaplan-Meier techniques will be used to plot both outcomes. Comparison of outcomes between the study arms will be based on a Cox regression model. The hazard ratio (HR) associated with the study arms will be derived from this model along with the associated 95% confidence interval (CI). A Cox regression model with intervention as the exposure and the co-primary endpoints and adjusted for the tumour stage and neoadjuvant treatment (stratification variables) will be used to assess the effect. A detailed description of the Cox regression model will be specified in the Statistical Analysis Plan (SAP). The p value for testing the null hypothesis that the HR between the interventions will be greater than or equal to 1.19 will be derived from this model by comparing the log-likelihood of the fitted model with the log-likelihood of a model where the HR between the groups is set to 1.19 by use of a likelihood ratio test.

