### **11.1 SAMPLE SIZE CALCULATIONS (CO-PRIMARY ENDPOINT – DISTANT METASTASES FREE SURVIVAL (DMFS) AND RELAPSE FREE SURVIVAL (RFS))**

The study design is a non-inferiority trial investigating whether short-term adjuvant immunotherapy, is non-inferior to long-term adjuvant immunotherapy (standard of care) with a non-inferiority margin (4.0%) being accepted as being clinically appropriate in this study population.

Assumptions for the sample size calculation:

- DMFS at 2 years was 88.1% for stage IIb-c patients (Keynote 716 study) (1)
- DMFS at 2 years was 70% for stage III-IV patients (Checkmate 238 trial) (2)
- DMFS for the sample size will be based on these two measurements with a conservative estimate of 75.0% at 2 years and assuming same rates for RFS.
- Power = 80%
- Alpha level = 5%
- Non-inferiority Margin = 4%
- Accrual time = 48 months
- Follow up time = 60 months

Assuming a 4-year accrual and 5-year follow-up duration, a sample size of 1872 patients (936 in each study arm) will have 80% power (90% for each endpoint, which corresponds to a total power of 81%) with one-sided 95% confidence to declare non-inferiority with a margin of 4.0% (i.e., from 75% to 71.0% in the observation group) based on a 1:1 randomization with a corresponding HR of

1.19. The sample size may be either re-estimated or the non-inferiority boundary adjusted if the number of patients lost to follow-up is of concern.

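### The primary Cox model adjusts for two factors and calls them the stratification variables, but randomisation is stratified on four

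*Protocol*

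**What the plan says.** Protocol section 8.1 (Randomization procedure) allocates 1:1, "stratified according to tumour stage, and neoadjuvant treatment given or not, type of neoadjuvant treatment (PD-1 inhibitor or ipilimumab + nivolumab"), and adds "pathological response (partial or non-response) after neoadjuvant treatment". That makes four factors, each listed separately.

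Protocol section 11 (Statistical methods) makes the Cox model the basis of both co-primary comparisons, "adjusted for the tumour stage and neoadjuvant treatment (stratification variables) will be used to assess the effect". It names two factors and labels them as the stratification variables. The same paragraph tests the "null hypothesis that the HR between the interventions will be greater than or equal to 1.19" by a likelihood ratio test in this model, makes the per-protocol set primary, and leaves the detailed description of the model to the SAP.

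Section 11.1 derives the margin from 2-year survival of 75% falling to 71%, using a "conservative estimate of 75.0% at 2 years and assuming same rates for RFS".

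**The concern.** The usual principle is to analyse as randomised: factors that restrict the allocation belong in the primary model. Here the two lists disagree. An SAP that follows section 11 will not match the randomisation, and one that follows section 8.1 will depart from the protocol.

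Two things are at stake.

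- **Non-collapsibility.** Leaving a prognostic covariate out of a Cox model moves a non-null HR toward 1 even when the covariate is balanced. Type I error in a non-inferiority test is judged at HR 1.19, where such a pull favours declaring non-inferiority.
- **Balance in the analysed set.** Stratification balances the randomised patients, but the primary set is per-protocol. Exclusions can differ by arm and by response, so balance on the omitted factors is not guaranteed there.

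**Working it through.** **1. The two lists side by side**

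| Factor | Randomisation (8.1) | Primary Cox model (11) |
|---|---|---|
| Tumour stage | yes | yes |
| Neoadjuvant given or not | yes | yes |
| Neoadjuvant regimen | yes | not named |
| Pathological response | yes | not named |

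This step needs no assumption.

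**2. The plan's own figures**

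- Margin: ln 0.71 / ln 0.75 = 1.1905, which matches 1.19.
- Power: the exponential hazard is −ln 0.75 / 2 = 0.144 per year. With 4 years of uniform accrual and 5 further years, the event probability is 0.630, or 1179 events from 1872 patients. Power at one-sided 5% is Φ(ln 1.19 × √1179 / 2 − 1.645) = 91.0%. The protocol states 90% per endpoint.

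**3. Size of the pull if 1.19 is taken as the HR conditional on all four factors**

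The protocol gives neither the neoadjuvant share nor the prognostic strength of regimen or response, so all inputs below are assumptions.

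*Large-sample Cox fits.* Assumed: 20 to 60% neoadjuvant, half of them non-responders with 2 to 3 times the hazard, regimen HR 0.75. The error rate is Φ(ln(HR full / HR reduced) / (2/√d) − 1.645), with d = 1880 × 0.25 = 470 events at 2 years or 1880 × 0.630 = 1184 with full follow-up.

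- 2-year data: HR lower by 0.00 to 0.007; error 5.0 to 5.7%.
- Full follow-up: HR lower by 0.002 to 0.019; error 5.3 to 8.4%.
- Example near the top: HR 1.174 against 1.192. ln(1.192/1.174) = 0.0152, and 2/√1184 = 0.0581. Φ(0.262 − 1.645) = 8.3%.

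*Simulated trials.* 3000 trials of 1880 patients per scenario, block-randomised within all strata, with 5 to 9 years of follow-up. Stage IIb-c is set at 88.1% at 2 years, with stage HR ln 0.70 / ln 0.881 = 2.8. Stage III–IV is assumed to be 75% of patients, with neoadjuvant use confined to it. Half of the neoadjuvant patients are non-responders and half are on each regimen.

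| Scenario (neoadjuvant share of all patients; response HR; regimen HR) | HR, two-factor vs four-factor | False non-inferiority at 1.19 | Non-inferiority declared at 1.00 |
|---|---|---|---|
| Weak (15%; 1.5; 1.3) | 1.189 vs 1.190 | 4.9% vs 4.5% | 91.7% vs 91.4% |
| Middle (30%; 2.0; 1.5) | 1.185 vs 1.192 | 5.9% vs 4.7% | 92.6% vs 92.2% |
| Strong (45%; 3.0; 2.0) | 1.166 vs 1.189 | 9.1% vs 5.7% | 94.6% vs 93.2% |

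The Monte Carlo standard error of the error rates is 0.4 to 0.5 points. At a true HR of 1.00 both models give 1.00, so there is no pull there.

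**4. What HR does the stated margin imply inside an adjusted model?**

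The 75% and 71% are whole-population rates. From 0.881(1 − π) + 0.70π = 0.75, the stage III–IV share is π = 0.131/0.181 = 0.72.

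- *Stage alone.* Let S be the 2-year survival of stage IIb-c in the control arm. 0.28·S + 0.72·S^2.8 = 0.75 gives S = 0.880. Replacing S by S^h and setting the sum to 0.71 gives h = 1.195.
- *All four factors.* The same calculation with 20/40/60% neoadjuvant, non-response HR 2/2.5/3 and regimen HR 0.75 gives 1.198/1.204/1.211.

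So with four-factor adjustment, the conditional HR that corresponds to a 4-point loss lies above 1.19. In simulations calibrated to 75% versus 71% under these scenarios, the two-factor model gave 1.186 to 1.196 on 2-year data and 1.190 to 1.195 with full follow-up (Monte Carlo standard error 0.005 to 0.009). That is close to 1.19, though too coarse to exclude a small remaining shift.

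**The case against.** The strongest reply has four parts.

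- **The SAP will settle it.** The protocol says "A detailed description of the Cox regression model will be specified in the Statistical Analysis Plan (SAP"), and coding and pooling of levels are normal SAP content. This stands for coding and pooling. It does not cover the covariate list, which section 11 itself states and labels as the stratification variables.
- **Neoadjuvant treatment is shorthand for all three neoadjuvant factors.** Regimen and response exist only among neoadjuvant patients, and the parenthesis suggests an intent to adjust for whatever was stratified. This is possible but strained: section 8.1 lists the three separately, and response is not a treatment. If shorthand was meant, the same sentence cures it.
- **The error inflation is not established.** A reader might infer from the strong scenario that the primary test is anti-conservative at 8 to 9%. The documents do not support that. They give no neoadjuvant share and no prognostic strengths, and some of their text points to a limited share. Complete and near-complete responders are excluded (section 7.2), section 8.2 puts that group at more than 60% after combination treatment, and section 3 says practice differs by country. The co-primary endpoints are set at 2 years (section 9.1), where the assumed-input error is at most 5.7%. This part stands.
- **The margin is marginal.** Because 1.19 comes from overall rates, part of the shift reflects which HR the margin refers to rather than bias. This also stands. It does not defend the two-factor model as such, which is neither the unadjusted comparison nor the as-randomised one.

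**Conclusion.** The mismatch between sections 8.1 and 11 is a matter of text and holds without assumptions: four factors restrict the randomisation, and two are named in the primary model under the label of stratification variables.

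The consequence for the HR is conditional. It needs omitted factors that are prognostic and a true HR above 1. On 2-year data, or with few neoadjuvant patients, it is negligible. With full follow-up, 45 to 60% neoadjuvant and a threefold hazard in non-responders, it reaches 3 to 4 points of one-sided error if 1.19 is read as a fully conditional HR, and less if it is read as the whole-population margin from which it was derived. It would be wrong to conclude that the test as written is biased toward non-inferiority by a known amount.

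This is an almost free improvement, not a threat to the trial. Matching the analysis to the randomisation and protecting the per-protocol comparison from imbalance on response and regimen are sufficient reasons to make it.

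**What to change.** In section 11, replace the two named covariates by the factors as randomised: tumour stage plus one combined neoadjuvant variable with levels none, PD-1 inhibitor with partial response, PD-1 inhibitor with non-response, ipilimumab + nivolumab with partial response, and ipilimumab + nivolumab with non-response. State whether these enter as covariates or as strata, and fix before any results are seen how levels with few events are pooled. If regimen and response are left out on purpose, say so, give the reason, and drop the label that calls the remaining two the stratification variables. It would also help to state whether 1.19 is meant as a conditional or a whole-population HR.

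The cost is one sentence in the protocol, carried into the SAP. The data are already in the randomisation system, and the sample size need not change. In the simulated scenarios, power at HR 1.00 fell by 0.3 to 1.4 points with the fuller model and stayed above 91%.
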